## Abstract

**Background:**

Only half of those living with Alzheimer’s disease in France are currently diagnosed, and only one patient in three is supported during the early stages of dementia. This study aims to evaluate three cognitive tests for their predictive ability to diagnose mild cognitive impairments and Alzheimer’s disease and related disorders. For people aged 65 years or over, presenting with a memory complaint, these tests can be performed easily during a preventative consultation.

**Method/design:**

The EVATEM (*évaluation des troubles de l’équilibre et de la mémoire* (evaluation of balance and memory problems)) cohort study was designed to prospectively assess the predictive value of tests for the diagnosis of mild cognitive impairments and Alzheimer’s disease in elderly subjects aged 65 years or over. Subjects were recruited from three health examination centers that are part of the French health insurance system. If a memory complaint was identified (using a dedicated questionnaire), the five-word test, the cognitive disorders examination test and the verbal fluency test were administered during a preventative consultation. A memory consultation was performed at a University Hospital to diagnosis any potential cognitive disorder and a one-year follow-up consultation was also scheduled. We recorded 2041 cases of memory complaint at our Health Examination Centers. Cognitive tests were refused by 33.6% of people who had a memory complaint. The number of subjects sent to a University Hospital memory consultation was 832 and 74.5% of them completed this consultation. The study population therefore includes 620 subjects.

**Discussion:**

Tests for the early diagnosis of a mild cognitive impairment or Alzheimer’s disease and related disorders should be used in centers dedicated to disease prevention. These should guide subjects with memory impairment to full memory consultations at hospitals and improve the access to early medical and behavioral support.

**Trial registration:**

ClinicalTrials.gov:NCT01316562

## Background

In 2011, an estimated 5.4 million Americans were living with Alzheimer’s disease (AD); this number is expected to grow to 7.7 million by 2030. In France, AD affects about 800,000 people over the age of 75 [1]. The pathophysiological process of Alzheimer’s disease is known to begin several years before the onset of cognitive symptoms. This “pre-clinical” stage is regarded as the most efficient stage for therapeutic intervention but it is still an active domain of research [2,3]. Although the benefit of early diagnosis is still debated, early identification of a cognitive impairment could lead to earlier treatment, better care management and improved understanding of the disease [4,5]. Being able to inform the patient and their family about the disease, at a time when the patient can still fully comprehend their illness, may ensure a better long-term quality of life for patients and caregivers as well as help to limit crisis situations. Only half of those living with AD in France are currently diagnosed, and only one patient in three is supported during the early stages of dementia [6]. According to the PAQUID cohort study [7], the average Mini-Mental State Examination (MMSE) [8] score at the diagnosis of dementia is approximately 19 (maximum score possible: 30). This score corresponds to a moderate stage of the disease. The average time taken to diagnose dementia in France is estimated to be 24 months; this is relatively long as the average time taken in Europe is estimated at 20 months and, in Germany, 10 months [9]. Cognitive impairment diagnoses are performed by specialized multi-disciplinary teams during memory consultations. Diagnoses carried out in France since 2009 are listed in the Alzheimer National Bank (created under the 34^th^ measure of the National Alzheimer’s Plan (2008–2012)). Of the 118,776 patients observed in 320 memory clinics (MC) during 2010, Mild Cognitive Impairment (MCI) was diagnosed in 8.4% of the cases [10]. The health examinations centers (HEC) perform 550,000 periodic examinations dedicated to screening, prevention and health education each year; people over 60 years old represent about 20% of those receiving periodic examinations. Senior health examinations [11,12], set up in 2006, focus on screening for fall risk without particular attention to memory complaints.

A study of 1020 people aged 60 years or over, at six HEC, found a prevalence of memory complaints in 35.1% of cases [13,14]. A resulting 12.3% of the patients were sent to MC following neuropsychological tests such as the MMSE. These types of assessments are difficult to perform routinely during a preventive consultation.

Studies have therefore been set up to identify simple tests, feasible in consultation at HEC with elderly patients expressing a memory complaint, that have good predictive power to diagnose MCI [15-18] and AD and related diseases.

The EVATEM (é*valuation des Troubles de l’équilibre et de la mémoire* (evaluation of balance and memory problems)) study aims to evaluate the predictive values (PV) of three cognitive tests for the diagnosis of MCI and AD and related disorders in community-dwelling elderly people. The secondary objective is to assess the relationship between falls and cognitive impairments.

## Methods/design

### Study design

This is a prospective multicenter cohort study with a one-year follow-up. Tests were carried out at two types of medical organizations: HEC and MC. HEC are structures belonging to the French health insurance system which offers check-ups and screening for the prevention of health conditions, health education and actions, and chronic disease support. This is a free check-up and priority is given to frail or vulnerable people. MC (as defined by the circular issued by the *Direction Générale de l’Offre de Soins* (DHOS) (general directorate for healthcare provision) on 16^th^ April 2002) offer consultations and day hospitalizations which are dedicated to medical diagnostics, follow-up and nursing (treatments both with and without the administration of drugs). MC are responsible for research on AD and related disorders, participate in academic training and coordinate an interregional plan for local memory consultations.

The three HEC which participated in the EVATEM study are located in three French cities: Lyon Angers and Saint-Etienne. The diagnostics were performed through three MC in the academic hospitals of these three cities. The study is composed of several steps (Figure 1). Patients with a memory impairment were identified at HEC using questionnaires and cognitive tests during periodic health examination at T0. Memory consultations to diagnose MCI and AD and related disorders were carried out at MC according to a standardized neuropsychological evaluation and complementary exam at T0. A one-year follow-up exam, at T1, was scheduled for each of the patients.

**Figure 1 F1:**
[figure not shown]
An outline of the steps in the EVATEM study.

### Ethical and legal considerations

All EVATEM subjects gave their informed consent to participate in this study. Their participation or refusal had no effect on the usual nursing performed at the HEC. The study protocol has been reviewed and approved by an ethics committee CPP Sud-Est III (*comité de protection des personnes Sud-Est III* (Persons protection comity of South-East III)) on the 7^th^ of July 2009. All procedures are in compliance with the Helsinki declaration. Data processing is approved by the CNIL (*commission nationale de l’informatique et des libertés* (National Commission for Informatics and Liberties)) under n°1362516.

EVATEM study has been registered in the clinical trials (Current Controlled Trials NCT01316562 NCT01316562).

### Population

Subjects were selected during free periodic health examinations in one of the three health examinations centers that participated in this study. These HEC were located to the cities of Lyon, Angers and Saint-Etienne.

Patients could be included if they were 65 years of age or older, lived at home or in a non-medical institution, volunteered to participate to a periodic health examination and if a memory impairment concern was identified (either by the patient themselves or by a member of their family).

Patients were excluded from the study if they had dementia, an inadequate level in French language ability, to a sensory deficiency which would compromise their evaluation.

### Sample size

We calculated the required sample size need to detect an expected sensitivity and specificity of 0.9 with the cognitive tests used in the HEC.

We set the minimum acceptable lower 95% confidence limit at 0.75, with a 0.95 probability.

Using the table of Flahault *et al.* 70 confirmed cases were required [19]. The number of controls required was calculated to be 513 with the equation: N controls = N cases [(1-P)/p] [19]; where p was the expected prevalence of MCI or AD and related disorders (we supposed this to be 12% [13])_._ The total target sample size was therefore 583.

We predicted the loss of subjects between examinations in the HEC and the MC to be 30% and so aimed to recruit 833 subjects. Actual recruitment was consistent with these estimates.

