### Statistical analysis

Baseline characteristics of the subjects (for example, age and sex) will be described as above. Continuous variables will be summarized by the mean and standard deviation or the median and interquartile range (as appropriate). Categorical variables will be summarized as proportions of each category.

Socio-demographic and clinical comparisons will be performed between three groups (normal, MCI and dementia subjects). Group proportions will be compared using Pearson’s chi-squared test. The means of these groups will be compared using an Analysis of Variance (ANOVA) with parametric and nonparametric tests, depending on the distribution of the variables. We will study the relationship between the result of each cognitive test performed at HEC and the diagnosis confirmed by the memory consultation. A Receiver Operator Characteristic (ROC) curve will be generated for each cognitive test, using MCI and AD and related disorders diagnosis as references. The optimum threshold, providing the best compromise between sensitivity and specificity, will therefore be determined. Predictive and negative values, as well as positive and negative likelihood ratios, will be calculated. We will use a binary or multinomial logistic regression to determine which test, or combination of cognitive tests, are the most predictive for MCI and AD and related disorders diagnosis. Models will be adjusted for potential confounding variables.

A p value less than 0.05 will be considered as statistically significant.

Statistical analyses will be performed using SPSS (Statistical Package for the Social Sciences) version 17.0 for Windows (SPSS Inc., Chicago, Illinois, USA).

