## Discussion

The EVATEM study will identify which one, or which combination, of these studied tests are the most predictive of MCI and AD and related disorders. This will provide a recommendation as to which should be performed on elderly patients reporting a memory complaint during a health examination at HEC.

The age for inclusion selected for the EVATEM study was 65 years old and more as the prevalence of AD is low before the age of 65 years [53]. This age criterion was also used in the PAQUID study [54] and in a three city study [55].

HEC recruit elderly patients from those listed in the files of the French health insurance system. Previous studies have compared elderly individuals using HEC to those of the general population of the same age. It appears that people over 60 years old who consult at HEC are more likely to be young male seniors (60 to 70 years old), living in couples, individuals with a healthy lifestyle (lower tobacco consumption, lower alcohol consumption and more physic activity) and those that consult more frequently than the corresponding general population (data unpublished, CETAF). However, it was previously thought that the population attending HEC was not fundamentally different from the general population of elderly persons aged over 60 years who were living at home and not suffering from disabilities.

The fact that patients agreed to participate to a periodic examination suggests that they take an interest in their health and may therefore also be more likely to attend cognitive impairment screening. Use of the Q1 questionnaire may lead to a self-selection bias associated with the fear of diagnosis, especially if another family member is suffering from AD. Representations of this type of disease and people with AD in our society are extremely negative. Consequently, patients may delay, as long as possible, addressing the issue of a disease that “crystallizes all the fears associated with aging” [6]. Societal representations lead to denial behavior and avoidance of medical consultations as the fear of diagnosis is associated with a set of losses including identity and dignity [56,57]. The administration of Q2 by doctors from Lyon led to a high selectivity in the screening of memory complaints. It will be interesting to compare the diagnostic and predictive values of the tests that result from these two groups.

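### The plan promises to say which of three tests is most predictive, but its stated analysis gives no estimate, and no uncertainty, for the difference in accuracy between tests given to the same subjects

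*Protocol article*

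**What the plan says.** **Sample size (Methods/design).** The planning value is "an expected sensitivity and specificity of 0.9 with the cognitive tests used in the HEC". The criterion is "We set the minimum acceptable lower 95% confidence limit at 0.75, with a 0.95 probability". From this, "70 confirmed cases were required"; controls follow from an assumed prevalence of 12%, and "The total target sample size was therefore 583". The section mentions no difference between tests and no comparison of one test with another.

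**Statistical analysis (Methods/design).** "A Receiver Operator Characteristic (ROC) curve will be generated for each cognitive test, using MCI and AD and related disorders diagnosis as references". A cut-off is then chosen for each test, and predictive values and likelihood ratios are calculated. A binary or multinomial logistic regression, adjusted for potential confounders, is to show which test or combination predicts the diagnosis best. The general significance level is 0.05.

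**Discussion.** The opening sentence reads: "The EVATEM study will identify which one, or which combination, of these studied tests are the most predictive of MCI and AD and related disorders". The next sentence says that this will yield a recommendation on what to perform at the health examination centers.

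**Design.** Abstract and Examination procedure: the five-word test, CODEX and verbal fluency are all given to the same subject at the same consultation.

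**The concern.** Deciding which of three tests is most predictive is a comparison between tests. Because every subject takes all three, it is a paired comparison, and the quantity needed is the difference in accuracy between two tests, with an interval that allows for their correlation.

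The stated steps do not produce it. Three separate ROC curves give three accuracies, but intervals drawn one test at a time do not give the uncertainty of a difference between correlated tests. A joint logistic regression answers another question: whether a test adds information once the other tests and the adjusting variables are in the model. A weaker test can add information, and a strong one can look redundant beside a test that overlaps with it. Neither result says how much more accurate one test is than another.

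At stake is the recommendation to the centers. If the tests are close, a chance ordering could be taken as a finding, and the reader would have nothing by which to judge it.

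**Working it through.** **1. What the sample size covers.** Inputs from Sample size: true value 0.90, lower 95% limit at least 0.75, probability 0.95. Sidedness is not stated; an exact one-sided limit reproduces the figure.
- n = 70: at least 59 correct are needed for the exact one-sided 95% lower limit to reach 0.75. P(X ≥ 59 | n = 70, p = 0.90) = 0.956.
- n = 69: also 59 needed; the probability is 0.920. So 70 is the first size to meet the criterion.
- Controls: 70 × 0.88/0.12 = 513.3, stated as 513. Total: 70 + 513 = 583. Recruitment: 583/0.70 = 832.9, stated as 833.

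All the figures reproduce. With 513 controls the specificity criterion is met with probability near 1, so sensitivity is the binding part. The 0.95 concerns one proportion of one test at a time.

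**2. What the stated analysis delivers.**

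| Question | Stated step that answers it |
|---|---|
| How accurate is each test alone? | ROC curve, cut-off, predictive values, likelihood ratios |
| Does a test add information beside the others? | Adjusted logistic regression |
| How much more accurate is test A than test B in the same people, and how sure is that? | None |

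The promise in the Discussion depends on the third row.

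**3. Illustration: how well 70 cases separate two sensitivities.** The documents give no rival sensitivity and no between-test correlation, so both are assumptions shown as ranges. The better test is set at the plan's 0.90.

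For sensitivities p1 and p2 with within-case correlation ρ:
- P(both positive): p11 = p1·p2 + ρ·√[p1(1−p1)·p2(1−p2)]
- Discordant probabilities: p10 = p1 − p11, p01 = p2 − p11

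Example, 0.90 vs 0.80 with ρ = 0.3: p11 = 0.72 + 0.3 × 0.3 × 0.4 = 0.756, so p10 = 0.144 and p01 = 0.044.

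McNemar power (asymptotic test, two-sided 5%) was obtained by summing over the number and split of discordant pairs in 70 cases:

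| Sensitivities | ρ = 0 | ρ = 0.3 | ρ = 0.5 |
|---|---|---|---|
| 0.90 vs 0.85 | 0.14 | 0.16 | 0.22 |
| 0.90 vs 0.80 | 0.38 | 0.49 | 0.64 |
| 0.90 vs 0.75 | 0.66 | 0.80 | 0.94 |

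The exact McNemar test gives 0.09–0.13, 0.30–0.52 and 0.57–0.89 over the same range of ρ.

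**4. The same point as an interval.** The approximate 95% half-width of a paired difference d is 1.96·√[(p10 + p01 − d²)/n]. For 0.90 vs 0.80 and n = 70:
- ρ = 0: 1.96·√[(0.18 + 0.08 − 0.01)/70] = 0.117
- ρ = 0.5: 1.96·√[(0.12 + 0.02 − 0.01)/70] = 0.084

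A true gap of 10 points would be reported with about ±8 to ±12 points.

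**5. Sensitivity to the number of cases.** The 70 depends on 12% prevalence. If, as an assumption, 20–30% of the 620 subjects seen were cases (124–186), power over ρ = 0 to 0.5 would be 0.23–0.55 for 0.90 vs 0.85, 0.61–0.98 for 0.90 vs 0.80 and 0.89–1.00 for 0.90 vs 0.75.

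**The case against.** **The sample size is not wrong.** The Background states the aim as evaluating the predictive values of three tests. Sizing each test against a minimum fits that aim, and sizing for estimation rather than for every later comparison is ordinary practice. This stands in full. A reader might infer that the 0.95 was meant to cover the choice among tests, and that the McNemar powers fall short of it. The documents do not support that. The 0.95 is the probability that a single confidence limit clears 0.75; the protocol sets no power target for a between-test difference, so subtracting one from the other compares unlike quantities. Nor does a common planning value of 0.90 amount to a hypothesis that the tests are equal.

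**The power figures rest on assumptions.** They run from 0.14 to 0.94, and more cases would raise them. They also concern sensitivity at a cut-off, not AUC, which uses cases and non-cases together and for which no power was calculated. This stands, and is why they serve only as illustration.

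**The regression is a comparative step, and the text does not say that tests will be chosen by p-value.** Correct. A reader might infer such a rule from the general 0.05 sentence, but the article does not state one. The regression still gives no difference in accuracy between tests.

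**Methods of comparison belong in an analysis plan.** In part. The choice between DeLong and bootstrap can be left there. But the article itself states both how the best test is to be determined and the conclusion to be drawn, and the first does not supply what the second needs.

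**A center may reasonably choose between similar tests on the best estimate or on feasibility.** Agreed. No rule that an interval must exclude zero before a test is named is needed here; the interval only has to be shown.

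**Conclusion.** The point holds as an improvement to the analysis and the wording, not as an error in the sample size. Statistical analysis and Discussion commit to determining the most predictive test or combination, while the stated steps estimate no paired difference in accuracy and attach no uncertainty to the ranking. That follows from the text alone and needs no assumption.

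How much it matters depends on how far apart the tests are. At the planned 70 cases, gaps of 5 points in sensitivity would usually go undetected and gaps of 10 points often would. A 15-point gap would be detected in most scenarios, and with good power if the tests are strongly correlated. These statements rest on the assumed rival sensitivities, correlations of 0 to 0.5 and the planned case number. The single-test accuracy estimates are unaffected.

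**What to change.** 1. **Statistical analysis.** Add, on the same subjects: pairwise AUC differences between the three tests with 95% confidence intervals, by a method for correlated ROC curves (DeLong or paired bootstrap); paired differences in sensitivity (cases) and specificity (non-cases) at the chosen cut-offs, with intervals; and the AUC gain of any combination over the best single test, with an interval.
2. **Discussion.** Replace the unconditional promise in the opening sentence with wording that reports the ranking together with these intervals and says when the tests are not distinguished.
3. **Sample size (optional).** Add one sentence: the 0.95 refers to the accuracy of a single test, and the comparison among tests was not separately powered.

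The cost is a few lines of analysis on data already being collected. Inclusion closed at the end of 2011, and nothing here requires more subjects. The downside is that the study may have to report that the tests could not be separated.

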### Data collection

1. Senior health periodic examination at HEC

a. Socio-demographic data

Age, sex, marital status, address, economic affluence and vulnerability level (evaluated with the EPICES score, the individual index of deprivation used at the HEC [20]) were recorded.

a. Clinical data

We recorded weight, height, the number of different daily therapeutic groups attended, psychotropic dose (established by asking the patient or reading their last prescription), autonomy (evaluated by testing four activities of daily life [21]), and mood (evaluated using the Mini-Geriatric Depression Scale (mini-GDS) [22]).

a. Para-clinical data

Data recorded included long sighted visual acuteness (evaluated using the Monoyer scale), an evaluation of balance and walking (using tests such as the Timed Up and Go (TUG) [23] and the imagined TUG), patient proprioception sensitivity (measured using the diapason test), and the results of the handgrip test, unipodal position evaluation, chair rising, temporal analysis of walking and posture analysis (at the HEC of Lyon and Angers).

a. Memory complaint

A self-questionnaire composed of binary questions (Q1) was used to assess memory at the HEC Angers and Saint-Etienne. A questionnaire (Q2) was carried out by the doctor at the HEC of Lyon (Table 1). At least one positive answer to the questionnaire was required for the subject to be included in the study.

a. Cognitive testing performed

The EVATEM study assessed Dubois’ five-word test [24], the cognitive disorders examination test (CODEX) [25,26] and the verbal fluency test [27]. These tests were chosen as they assess verbal memory, temporal and spatial orientation and executive function but are straightforward and rapid.

Dubois’ five-word test is an episodic memory test where subjects are asked to learn five words belonging to different semantic groups and lacking phonetic similarity (for example: beverage, cooking tool, vehicular, building and insect) with control of the encoding. The test is built in such a way that it enables differentiation between symptoms of hippocampus damage (associated with AD) and common memory impairment; it includes immediate free recall exercises and postponed free recall activities. In the case of recall difficulty, a cue is suggested.

The CODEX test is designed to detect dementia in elderly subjects. It is a very simple and quick test (taking less than three minutes) and can be performed by doctors who are not specialized in the evaluation of memory or other cognitive functions. This test consists of two stages: the three-word test and simplified clock test [28] are carried out before the MMSE (five questions of spatial orientation). In the EVATEM study, the three-word test, the simplified clock test and the five spatial orientation questions were all performed.

The test of verbal fluency measures the capacity of a subject to generate a list of words belonging to the same semantic category (animals), and a list of words starting with the same letter (P), within a time limit of two minutes. This test assesses semantic memory and executive memory functions. In the case of a neurodegenerative disease, particularly in AD, semantic fluency seems to be impaired and this may be associated with possible damage to the semantic memory stock [29].

2. Neuropsychological evaluation performed at MC

The cognitive tests described below were performed routinely in MC. Episodic memory was assessed using the following tests: a free and cued recall test with 16 items (test adapted from Grober and Buschke [30]), the DMS48 [31], the Signoret battery for mnesic efficiency (BEM 144) [32] and the Birmingham Object Recognition Battery (BORB) [33]. Executive abilities were assessed using the Frontal Assessment Battery (FAB) [34], Baddeley’s dual task test [35], the Wechsler Adult Intelligence Scale III (WAIS III) [36,37], the Trail Making Test (TMT) [38], the STROOP test (GREFEX version) [39] and semantic verbal and literal fluency tests (using ‘P’ and ‘Animals’; a two minute test)[27]^.^ Instrumental efficiency was evaluated by gestural praxis assessment (symbolic gestures, pantomimes and abstract gestures), the Rey complex figure [40], the picture naming test (DO 80) [41] and the Visual Object and Space Perception Battery (VOSP) [42].

These tests were conducted by a neuropsychologist and lasted approximately 1.25 h.

**Table 1 T1:** Memory complaint screening questionnaires (Q1 and Q2)

**Q1: self-questionnaire**	**Q2: questionnaire administered by the doctor**
	During the six last months:
1. In the last six months, have any of your close relations suggested that you have a possible memory problem?	1. Have any of your close relations told you that you have memory problems?
2. Do you sometimes suffer from a lapse of memory during daily life?	2. Have you noticed any change in your memory?
3. Do you find it difficult to calculate?	3. Do you think that your memory now works less well than memory of other people of age?
4. Do you have difficulties finding your words?	4. Do you find it difficult to orientate yourself, or did you ever not recognize a place where your close relations have told you that you have been?
5. Do you have problems remembering new information?	5. Have you ever fogotten everything about an event (even if your close relations told you about it or you saw pictures about it)?
6. Do you find it difficult to focus?	

